### Sample size estimation

Sample size estimates were based on current recommended steps for calculating the minimum sample size necessary for prediction model development [28]. We anticipate enrolling approximately 100 football student-athletes at each site in their first year of data collection (with the opportunity for athletes to continue in the study during years 2 and 3). In years 2 and 3, we anticipate enrolling approximately 20 new student-athletes (primarily freshmen and transfers) at each site. This will result in an estimated enrollment of approximately 560 unique student-athletes after 3 years of data collection at each site and approximately 1200 player-years across all sites over the study period. Assuming, conservatively, an HSI prevalence of 15%, 5% attrition beyond graduation and transfer (e.g. season ending injuries), a within-subject correlation of 0.3 across study years, and an R^2^ (proportion of variability explained by model) of 20% we will be sufficiently powered to build an index HSI HAMIR index inclusive of approximately 10–12 candidate predictor parameters. Assuming 20% of the student-athletes who sustain an index HSI will re-injure, we conservatively estimate 180 student-athletes and 36 re-injuries will be available to develop a “re-injury” HAMIR index. Using the same modeling assumptions as for the index HSI, this will allow us to create a risk prediction model with up to 4 prediction parameters. The R package *pmsampsize* was used to estimate sample size requirements.

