### Planned statistical approach

Univariate and bivariate summary statistics and distributional plots will be examined for all candidate predictor variables to assess modeling and hypothesis testing assumptions; appropriate transformations will be considered. Candidate predictors for the prediction models will include standard demographic and clinical measures, muscle strain during sprinting (mechanical), and muscle morphology (e.g. muscle, scar and edema volume). The HAMIR index prediction models for index HSI injury and re-injury will be constructed using generalized estimating equations (GEE) for binary outcomes with a logit link, and will control for athletic-exposures. The correlation among individuals in repeated years will be accounted for using an appropriately identified correlation matrix structure. Clustering at the institution level will be considered and modeled as necessary. The mechanism for missing data will be assessed during the modeling stage and multiple imputation methods will be considered if necessary. The final risk prediction model will provide predictions of the average estimated risk of HSI (or re-injury) for an athlete given the values of model variables.

We will internally validate the models using standard internal validation criteria for the development of risk prediction models. The overall performance of the models will be assessed using the Brier score and calibration assessed using the Hosmer Lemeshow Goodness of Fit Chi-square, with a value < 20 representing sufficient calibration. We will assess discrimination with the c-statistic, with a value of 0.8 or higher indicative of excellent discrimination. Bootstrapping will be used to assess the potential optimization of the model.

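### The bootstrap is stated only as an assessment: nothing carries its result into the GEE coefficients, so high predicted risks will on average be overstated if the plan is followed as written

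*Protocol article*

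**What the plan says.** Under Planned statistical approach, the protocol article says both models will be "constructed using generalized estimating equations (GEE) for binary outcomes with a logit link". The output is an individual risk: "The final risk prediction model will provide predictions of the average estimated risk of HSI (or re-injury) for an athlete". Validation is introduced with "We will internally validate the models using standard internal validation criteria for the development of risk prediction models" and then itemised as the Brier score, a Hosmer–Lemeshow statistic below 20 and a c-statistic of at least 0.8. The last sentence gives the bootstrap its role: "Bootstrapping will be used to assess the potential optimization of the model".

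Under Sample size estimation, the article expects "approximately 560 unique student-athletes after 3 years of data collection at each site" and "approximately 1200 player-years across all sites over the study period", and about 10–12 candidate parameters for the index model. For re-injury it expects 180 athletes and 36 events, and says "this will allow us to create a risk prediction model with up to 4 prediction parameters". The sizing tool is pmsampsize.

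Neither section, nor the Discussion, mentions shrinkage, penalisation or recalibration.

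**The concern.** An ordinary GEE is an unpenalised fit. With limited events its coefficients are on average too large for new athletes, even when no predictor has been selected from the data. High predicted risks then come out too high and low ones too low. The bootstrap planned here is the standard means of measuring that error, but measuring it does not remove it. A calibration slope of 0.9 that is reported and not applied leaves the published equation about 10% too steep on the logit scale.

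What is at stake is the accuracy of the individual risk figure, and mainly of its upper end, where such a figure is most likely to be used. The re-injury model is the more exposed because it has few events.

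**Working it through.** **Inputs from Sample size estimation.** 1200 player-years; 560 unique athletes, which is the total over four sites, since 4 × (100 + 20 + 20) = 560; HSI prevalence 15%; attrition 5%; within-subject correlation 0.3; R² 20%, scale not stated; 10–12 index parameters; 180 athletes, 36 re-injuries and 4 parameters for re-injury. **Assumption:** a target shrinkage S of 0.90, which the article does not give.

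**Reproducing the plan's parameter counts.** The shrinkage criterion for a binary prediction model is n = P / [(S − 1) ln(1 − R²cs/S)], where P is the number of parameters and R²cs the Cox–Snell R².

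- Player-years after attrition: 1200 × 0.95 = 1140.
- Mean years per athlete: 1200/560 = 2.14. Design effect: 1 + 1.14 × 0.3 = 1.343. Effective n: 1140/1.343 = 849.
- Index model, R² read as Nagelkerke: the maximum R²cs at 15% prevalence is 0.571, so R²cs = 0.20 × 0.571 = 0.114. This needs 73.7 records per parameter, and 849/73.7 = 11.5. The stated 10–12 is reproduced.
- Re-injury model, R² read as Cox–Snell: 39.8 records per parameter, and 180/39.8 = 4.5. The stated 4 is reproduced.
- Event counts: 0.15 × 1200 = 180 and 0.20 × 180 = 36.

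The two counts match only under different R² scales. Cox–Snell throughout gives 849/39.8 ≈ 21 index parameters. Nagelkerke throughout gives 180/66.0 = 2.7, so 2 re-injury parameters. Both readings are therefore carried forward.

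**Expected size without correction.** The closed-form factor solves the same formula for S. The simulations fitted unpenalised logistic models to independent records at the effective n, with equal true effects and no predictor selection, and evaluated them in new data (300 to 600 replicates). Ranges are across separate sets of runs.

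| Model | R² reading | Closed-form S | Simulated slope | Mean excess, top 5% |
|---|---|---|---|---|
| Index, n 849, 12 parameters | Nagelkerke | 0.896 | about 0.89 (0.87–0.89) | about 4–5 points |
| Index, n 849, 12 parameters | Cox–Snell | 0.941 | about 0.90–0.91 | about 4 points |
| Re-injury, n 180, 4 parameters | Nagelkerke | 0.860 | about 0.82–0.86 | about 6 points (single runs up to 7) |
| Re-injury, n 180, 4 parameters | Cox–Snell | 0.910 | about 0.87–0.89 | about 4 points |

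In the top decile the direction is the same. For the index model (12 parameters, Nagelkerke), mean predicted risk was 47.0% against a true 43.1%. For re-injury it was 66.7% against 62.4% (Cox–Snell) and 55.4% against 50.6% (Nagelkerke). High-end risk was overstated in roughly 70–86% of simulated studies, depending on scenario and cut.

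**What shrinkage does to one prediction.** With mean risk 15% and S = 0.90, an unshrunken 40% becomes expit[logit(0.15) + 0.90 × (logit(0.40) − logit(0.15))] = 36.9%, and an unshrunken 5% becomes 5.6%.

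**After correction** (bootstrap slope applied, intercept refitted). The top-5% excess fell to about 0–0.6 points for the index model. For re-injury it fell to between under 0.5 and 2.0 points, with the larger values under Nagelkerke. The mean squared error of predicted risk fell in every scenario.

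**The case against.** The strongest objection is that the omission is inferred from a condensed article. A reader might infer that the plan makes uncorrected coefficients the HAMIR index and confines the bootstrap to assessment. The article says neither. It invokes standard internal validation criteria, and the Discussion refers to a study analysis plan that is not shown and could specify shrinkage. That stands, and it is why the point is conditional on following the text as written. It does not dispose of the point: the article does fix the purpose of the bootstrap, in a sentence that needs rewording anyway, and that is where the step belongs.

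Second, the parameter limits already hold expected shrinkage near 0.9, so the design has accepted some overfitting. This is correct and explains why the excess is only a few points. It limits the bias without removing it, and a means of removing most of it is already planned.

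Third, a reader might infer that every high-risk athlete's figure will be too high, or that the wrong athletes will be flagged. Neither follows. The excess is an average tendency, absent in a sizeable minority of simulated studies. Multiplying the linear predictor by one positive constant leaves the ranking and the c-statistic unchanged, and the article sets no risk threshold for action.

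Fourth, the Discussion calls the re-injury model preliminary and expects further testing. That tempers the claims made for that model, but it neither corrects its equation nor covers the index model.

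**Conclusion.** The point holds in conditional form. The only stated use of the bootstrap is assessment, and no step carries its result into the coefficients. Followed as written, the plan yields top-5% risks that are too high on average by about 4–5 percentage points for the index model (slope about 0.89–0.91) and about 4–6 points for the re-injury model (slope about 0.83–0.89).

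These sizes rest on the plan's R² of 20% under either scale, an exchangeable correlation of 0.3 handled through an effective n, equal predictor effects and no data-driven selection. The planned consideration of transformations and the choice of correlation structure from the data could add optimism. A lower R² would also enlarge the excess, but that is not the plan's assumption. The bias is modest and predictable, and correcting it costs little.

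**What to change.** Replace the bootstrap sentence under Planned statistical approach with the following, applied to both models:

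> Bootstrapping, resampling athletes and repeating every data-driven modelling step, will estimate optimism and the calibration slope; the final linear predictor will be multiplied by that slope and the intercept re-estimated, and the published HAMIR equations will be the shrunken ones.

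Resampling athletes rather than player-years keeps each athlete's repeated years together. If the full analysis plan already specifies shrinkage, the same sentence simply confirms it.

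The cost is a line or two of extra analysis on a bootstrap already planned; no new data are needed. The downside is that with about 36 re-injuries the estimated slope is imprecise. The re-injury correction is therefore approximate, right only on average, and may leave about 1–2 points of overstatement. The report should say so.

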## Discussion

The high incidence of HSI and recurrent HSI in American football continues to burden professional leagues in regards to athlete performance and financial loss. As such, there is a need to better understand the reasons for HSI injury and re-injury in these athletes so that appropriate risk reduction strategies can be created to ultimately reduce the incidence of HSI. The most appropriate strategies for reducing risk of HSI are likely multi-factorial and depend on risk factors unique to each athlete. To our knowledge, this study will be the largest-of-its-kind (1200 player-years) to gather detailed information on index and recurrent HSI, and will be the first study to simultaneously investigate the effect of morphological, biomechanical and clinical variables on risk of HSI in elite collegiate football athletes. The quantitative HAMIR index will be formulated to identify an athlete’s propensity for HSI, and more importantly, identify targets for injury mitigation, thereby reducing the global burden of HSI in elite American football players.

Because this is strictly an observational study, we cannot guarantee the same practices will occur across all sites (e.g., rehabilitation protocols, return to sport decisions), nor can we control against major program changes such as coaching and staff turnover across the duration of the study period or differences in practice and competition schedules between sites. However, these issues represent realistic variability in clinical care and sports seasons; we intend to account for site-to-site variability and athlete exposure when developing the HAMIR index. Moreover, each site has agreed to adhere to the same protocol for detailed data collection on injury management, and all MRI and IMU data will be processed at a central location. As is common to prospective cohort studies, there is the potential that we are unable to capture all protocolized timepoints on all enrolled athletes; however, the manual of operations addresses specific policies for site coordinators to follow to minimize potential missing data. Additionally, the study analysis plan proposes to assess any missingness in data collection and will account for it, as appropriate, in the analytic phase. Our ability to create a meaningful recurrent HAMIR index is entirely dependent on the number of recurrent HSIs observed during the study period. Risk factors for re-injury are largely unknown and no objective data are available to guide practitioners on return-to-play decisions following HSI. We estimate only being able to include up to 4 predictive parameters in such an index for recurrent HSI and this may or may not be sufficient to accurately predict re-injury risk. However, this information is urgently needed by practitioners and we will minimally be able to provide a preliminary predictive model that can be further tested as more re-injury data is captured in this population.

## Data Availability

Not applicable.

## Abbreviations

HAMIR: Hamstring Injury Index
HSI: Hamstring strain injury
IMU: Inertial measurement units
MRI: Magnetic resonance imaging
MTU: Muscle–tendon unit
NCAA: National Collegiate Athletic Association
D1: Division I
REDCap: Research Electronic Data Capture
HaOS: Hamstring Outcome Score
FASH: Functional Assessment Scale for Acute Hamstring Injuries
GEE: Generalized estimating equations
DCC: Data coordinating center
